### Transcranial random noise stimulation (tRNS)

During the active hf-tRNS session, participants will receive 0.75 mA (±0.375 mA) of tRNS (100–500 Hz) to their temporo-parietal regions via 2 saline-soaked (0.90 mol) 25 cm^2^ circular sponges, placed over TP7/P7 and TP8/P8 based on the International 10–20 System. The current will be delivered by a BrainStim stimulator (E.M.S. s.r.l.; Bologna, Italy) for 20 min per session, as in previous tRNS protocols (24, 26, 60–64). The impedance of the electrodes will be checked before and during the application of hf-tRNS to ensure that it remains below 10 kW. tRNS parameters are based on already published procedures (24, 55).

### Sham tES conditions

To control for potential placebo effects, participants during the sham condition will undergo the same procedures as those in the active conditions (active tDCS, active hf-tRNS). This includes using the same electrode positioning and tRNS/tDCS equipment turn-on time (30 s). Apart from this short stimulation, during the sham condition participants will not receive the real stimulation (0 mA) for the rest of the session.

Among all participants, half of them will undergo a sham tDCS session (with the same electrode positioning and tDCS equipment turn-on time), while the other half will undergo a sham tRNS session (with the same electrode positioning and tRNS equipment turn-on time).

All participants, their families and the evaluators will be blinded to the stimulation conditions.

### Reading tasks

Four different reading tasks (text – TEXT; high-frequency words – HF; low-frequency words – LF; non-words – NW) will be presented to the participants in the Italian language. Participants will be required to read aloud as quickly and accurately as possible.

TEXT derived from an Italian novel (65). Items in HF list and LF list were matched for Italian written word frequency, number of letters and syllables, bigram frequency (according to CoLFIS)^1^ and mean onset reaction time. To avoid the repetition effect, multiple versions of each reading task will be administered. This will include different versions presented at baseline (before stimulation) and during each stimulation session, resulting in a total of six versions across the study. The purpose of this approach is to minimize the impact of task familiarity. To control for the influence of fatigue, the order of the reading tasks will be counterbalanced between the three conditions (tDCS, hf-tRNS, and sham).

Regarding reading task characteristics, each TEXT will be composed of approximately 400 syllables, each list of HF will be composed of 30 high frequency words (over 70 syllables long), each list of LF will be composed of 30 low frequency words (over 70 syllables long), and each list of NW will be composed of 30 non-words (over 70 syllables long).

For each reading task (TEXT, HF, LF, and NW), both reading speed and accuracy will be measured and considered. Concerning TEXT reading accuracy, an error point will be assigned in presence of substitution, omission, and/or addition of syllables. A 0.5 error will be assigned in case of auto-correction during reading. The number of words correctly read will be considered, and the percentage of accuracy will be calculated via dividing the number of correctly read stimuli by the total number of stimuli presented and multiplying the result by 100. For the remaining tasks (HF, LF, NW), an error point will be assigned in presence of substitution, omission, and/or addition of syllables, while auto-corrections during reading will not be treated as errors. The number of errors will be considered, and the percentage of errors will be calculated via dividing the number of errors by the total number of stimuli presented and multiplying the result by 100.

Concerning reading speed, syllables per seconds (syll/s) will be considered by dividing the total number of pronounced syllables by the time taken to complete the reading task (in seconds) for all tasks (TEXT, HF, LF, NW).

To ensure that the six versions of each reading task (TEXT, HF, LF, and NW) are comparable in terms of difficulty for both accuracy and speed, a pilot study was conducted with a group of typically developing readers. This preliminary investigation helped determine that the task versions will be appropriately matched in difficulty across the different conditions (see Supplementary materials S3).

The primary outcome of the study will be the changes in TEXT reading accuracy during the active tDCS and active hf-tRNS sessions compared to the sham session (tDCS/tRNS), in comparison to the baseline measurement on Day 0. The primary outcome has been defined based on the results of Costanzo et al. (16), whereby a single session of active left anodal/right cathodal tDCS over temporo-parietal regions led to significant improvements on TEXT reading accuracy compared to control conditions.

Similarly, the secondary outcomes of the study will examine changes in TEXT reading speed, as well as changes in the accuracy and speed of the other reading tasks (HF, LF, and NW) during the active tDCS and active hf-tRNS sessions compared to the sham session (tDCS/tRNS), in comparison to the baseline measurement on Day 0.

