**Figure 1 fig1:**
[figure not shown]
Schedule of enrolment, interventions, and assessment: Recommendations for interventional trials (SPIRIT). tDCS, transcranial direct current stimulation; tRNS, transcranial random noise stimulation; TEXT, texts reading task; HF, high-frequency words reading task; LF, low-frequency words reading task; NW, non-words reading task.

The principal investigator will dispose of an emergency code for each participant that can be revealed in case of a compelling need, such as a serious adverse event that requires awareness of current interventions to handle the participant’s condition.

Immediately before each session (i.e., Day 1, Day 2, and Day 3) and during the maximum peak of tES effects [approximately 10 min after the start of stimulation; (58), participants will undergo an assessment that will include text, words and non-words reading]. The order of the tasks administered will be randomized and counter-balanced across participants. Each session will last approximately 35 min. This includes 10 min for the reading tasks conducted before the stimulation session, 20 min for the stimulation session (active or sham) combined with concurrent reading tasks (initiated after 10 min of stimulation), and 5 min for the administration of the safety and blinding questionnaire after the stimulation session. In any case, we will take into account the time spent reading the various reading tasks overall (i.e., TEXT, HF, LF, and NW) by each participant. In the event that a participant exceeds 10 min during pre-stimulation reading, we will begin administering the tasks in a way that ensures completion of the reading within the 20-min stimulation period.

At the end of the final session (Day 3), participants will be informed of their assigned condition (i.e., ABC, ACB, BAC, BCA, CBA or CAB) and provided with brief feedback on the results that emerged from each session (Figure 2).

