### Sample size

The sample size is calculated on the primary outcome by *a priori* analysis in G*Power, version 3.1.9.7 (The G*Power Team, Düsseldorf, Germany). Based on the study design and assumptions, the estimated results suggest that participants who receive a single session of active tDCS or hf-tRNS will demonstrate an improvement in TEXT reading accuracy compared to their baseline performance. On the other hand, participants who receive a single session of sham tDCS or sham tRNS are not expected to show a significant change in their performance compared to baseline. While the design of this project has never been employed in DD, we will refer to (i) a previous study by Costanzo and collaborators (16) who prove the effectiveness of a one-session active left anodal/right cathodal tDCS over temporo-parietal regions in a within-subject design; (ii) a study with similar features (e.g., one-session, sham-controlled experiment, comparing baseline vs. tDCS vs. tRNS vs. sham) assessing other cognitive functions (35).

Based on these previous results, to be cautious and conservative, we estimate a medium effect size (f) of 0.25. With an estimated *f* = 0.25, α value = 0.05 (i.e., probability of false positives of 5%), and *β* = 0.80 (i.e., at least 80% power), the sample size is 24 as calculated using a Repeated Measures-Analysis of Variance (RM-ANOVA) model with four within factors (i.e., baseline, active tDCS, active hf-tRNS, and sham).

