### Statistical analyses and expected results

The Shapiro–Wilk test will be used to test the normality of the data and Levene’s test for the homogeneity of variances. When data will be normally distributed and the assumption of homogeneity will not be violated, parametric analyses will be computed. When one assumption will not be met, non-parametric tests will be conducted or a log-transformation of the distribution will be applied. Sphericity will be verified by Mauchly’s sphericity test and when not met, Greenhouse–Geisser correction will be applied.

Chi-Square analyses will be used to compare the groups on demographic and safety and blinding measures (categorical variables).

Covarying for age, a preliminary analysis to test the effect of the four repetitions (Day 0, Day 1, Day 2, and Day 3) of the reading tasks (accuracy and speed of TEXT, HF, LF, and NW) will be conducted.

RM-ANOVA will be used to compare reading measures (TEXT, HF, LF, and NW accuracy and speed), separately, with conditions (Day 0, A, B, C) as a within-subjects factor and age as covariate.

*Post hoc* comparisons will be assessed using Tukey’s honest significance test.

Partial eta squares (η_p_^2^) will be used as measures of effect sizes.

We hypothesize that:

hf-tRNS will be at least as effective as tDCS in improving TEXT reading accuracy compared with sham condition (primary outcome);hf-tRNS and tDCS will improve performance in the remaining reading tasks (TEXT reading speed and HF, LF, and NW reading accuracy and speed) compared with sham condition;hf-tRNS and tDCS will be as safe as sham condition (i.e., neither tDCS nor hf-tRNS will induce severe AEs or lead to dropouts due to intolerance to stimulation);the blinding will be kept across the conditions.

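### Two baselines are in use: the outcomes and the RM-ANOVA take a single Day 0 score, which cancels from active versus sham and comes before all practice, while the pre-session scores are named in neither

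*Protocol article*

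**What the plan says.** All references are to the protocol article.

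**Baseline as the pre-session test.** Study design (text after Figure 1) schedules text, word and non-word reading "Immediately before each session (i.e., Day 1, Day 2, and Day 3) and during the maximum peak of tES effects". Reading tasks describes "different versions presented at baseline (before stimulation) and during each stimulation session, resulting in a total of six versions across the study". The abstract also says that reading is measured before and during each session.

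**Baseline as Day 0.** Study design labels the eligibility visit Day 0 (Baseline). The last paragraphs of Reading tasks define the primary outcome, and likewise the secondary outcomes, as changes "during the active tDCS and active hf-tRNS sessions compared to the sham session (tDCS/tRNS), in comparison to the baseline measurement on Day 0". Statistical analyses specifies an RM-ANOVA "with conditions (Day 0, A, B, C) as a within-subjects factor and age as covariate". Sample size uses a "model with four within factors (i.e., baseline, active tDCS, active hf-tRNS, and sham").

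**Related text.** The order of tDCS, hf-tRNS and sham is counterbalanced over Days 1 to 3. A preliminary analysis, adjusted for age, examines repetition of the reading tasks from Day 0 to Day 3. The hypotheses are worded against sham.

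**The concern.** The primary endpoint should have one reference point, and here the text gives two. The one written into the outcome and the model is the less useful of the two.

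- It is one score per child, shared by all three conditions, so it cannot adjust a comparison between conditions.
- It is always the first reading occasion and never stimulated, so its difference from the later sessions includes any practice gain.
- It sits inside the omnibus test on which the sample size is based.

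At stake are a clear primary endpoint, the meaning of a significant omnibus F or of a reported gain over baseline, and power that the pre-session scores could add at no extra data collection.

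**Working it through.** **Inputs from the document.** Effect size: "we estimate a medium effect size (f) of 0.25". Alpha 0.05, power 80%, N = 24, four repeated levels (all from Sample size). Expected pattern: both active conditions improve on baseline and sham does not.

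**Assumptions, not in the document.** Correlation between occasions rho = 0.5 (range 0.3 to 0.7), sphericity, equal variances, and the same-session correlations used in step 5. The age covariate is ignored in the degrees of freedom.

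**1. The plan's own figure.** With m = 4 levels, lambda = f² × N × m / (1 − rho), df1 = m − 1 and df2 = (N − 1)(m − 1).
- N = 24: lambda = 0.0625 × 24 × 4 / 0.5 = 12.0, df 3 and 69, power 0.817.
- N = 23: lambda = 11.5, power 0.797.

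So N = 24 reproduces at rho = 0.5. At rho 0.3 the answer would be 32, and at 0.7 it would be 15. With means (Day 0, tDCS, hf-tRNS, sham) = (0, d, d, 0), the SD of the means is d/2, so f = 0.25 corresponds to d = 0.5 SD.

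**2. Version count.** 3 sessions × (before + during) = 6, which is every version described. A Day 0 administration with its own version would make 7, and no version is named for Day 0. Yet the repetition analysis counts Day 0 as one of four repetitions of the same tasks.

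**3. Day 0 in the primary contrast.** (A − Day 0) − (C − Day 0) = A − C, exactly, child by child. The same holds for hf-tRNS.

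**4. Practice and the omnibus.** Suppose there is no stimulation effect and a gain of g SD at every session after Day 0, so the means are (0, g, g, g). The sum of squared deviations is 0.75g², and lambda = 24 × 0.75g² / (1 − rho).

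| g | lambda at rho 0.5 | Rejection, rho 0.5 | rho 0.3 | rho 0.7 |
|---|---|---|---|---|
| 0 | 0 | 5% | 5% | 5% |
| 0.3 | 3.24 | 28% | 21% | 45% |
| 0.5 | 9.00 | 68% | 52% | 90% |

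Under the same null (rho 0.5, g = 0.3 or 0.5), simulating the planned four-level Tukey comparisons gives about a 2% chance that either active condition is declared different from sham. That contrast is protected.

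**5. What the pre-session score could add.** Effect d = 0.5 SD, N = 24, two-sided 5%, different-session correlation 0.5. Unadjusted, the variance of A − C is 2(1 − 0.5) = 1.0 and power is 0.65 (23 df). Regressing A − C on preA − preC leaves variance 1.0 × (1 − r²), where r = (rho_w − 0.5)/(1 − 0.5) and rho_w is the same-session correlation. One degree of freedom is spent. The raw change score has variance 2 × 1.0 − 4(rho_w − 0.5).

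| rho_w | r | Variance, covariate | Power, covariate | Variance, change | Power, change |
|---|---|---|---|---|---|
| 0.5 | 0 | 1.00 | 0.65 | 2.0 | 0.38 |
| 0.7 | 0.4 | 0.84 | 0.72 | 1.2 | 0.57 |
| 0.8 | 0.6 | 0.64 | 0.83 | 0.8 | 0.75 |

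The raw change score beats no adjustment only when rho_w exceeds (1 + 0.5)/2 = 0.75.

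**6. Power of N = 24 without Day 0.** With means (0.5, 0.5, 0) at rho 0.5, lambda = 24 × (0.25 × 2/3)/0.5 = 8.0 on df 2 and 46, giving power 0.69 for the three-condition omnibus. A single unadjusted active-versus-sham contrast has 0.65.

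**The case against.** The strongest reply is that the stated hypotheses compare each active condition with sham, that order is counterbalanced and that Day 0 cancels, so practice cannot produce a false active-versus-sham result. This stands, and the 2% figure in step 4 bears it out. The 28% and 68% describe the omnibus F and not the primary hypothesis. A reader might infer that the primary efficacy claim is biased; the documents do not support that.

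Second, the plan has safeguards: matched versions and a preliminary repetition analysis. These stand as mitigation, but the repetition analysis has no stated consequence for the main model.

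Third, a reader might infer that Day 0 has no reading test at all, or that the pre-session scores are never analysed. Neither is established. The schedule and design figures are not shown, reuse of a version is not excluded, and the repetition analysis does not say which Day 1 to Day 3 scores it takes. What can be said is that no version is named for Day 0, and that the pre-session scores are named in neither the outcomes nor the RM-ANOVA.

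Fourth, a reader might infer that including Day 0 necessarily inflates the error term. It does not if all correlations are equal; that would need Day 0 to correlate differently from the sessions, and the documents give no correlations.

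Finally, omitting a covariate costs precision and does not bias the contrast. At a same-session correlation of 0.5 there is nothing to gain.

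**Conclusion.** The concern holds in this form. The article contradicts itself on what baseline means for its primary and secondary outcomes. The definition written into the model contributes nothing to active versus sham and exposes the omnibus F, and any gain over Day 0, to practice: 28% rejection for a 0.3 SD gain and 68% for 0.5 SD at rho 0.5, against a nominal 5%. The range over rho 0.3 to 0.7 is 21% to 45% and 52% to 90%. The active-versus-sham contrast is unbiased but forgoes a covariate that the trial already collects, worth between nothing and 18 percentage points of power (0.65 to 0.83) over the same-session correlations examined. N = 24 is arithmetically right for the four-level omnibus, but it does not give 80% power for the comparison named in the hypotheses: about 65% unadjusted at rho 0.5. All correlations and practice gains are assumptions.

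**What to change.** 1. Reconcile the baseline definition across Study design, Reading tasks, Sample size and Statistical analyses, and state what reading test, in which version, is given on Day 0.
2. Define the primary and secondary outcomes as the score during stimulation, with that session's pre-stimulation score as its baseline.
3. Analyse three conditions (tDCS, hf-tRNS, sham) with the child-centred pre-session score as a time-varying covariate, in preference to a raw change score.
4. Base the conclusion on the active-versus-sham contrasts. Report Day 0 descriptively only.
5. Restate the power of N = 24 for that contrast: about 65% unadjusted at two-sided 5% and rho 0.5 (three-condition omnibus 69%), with the covariate gain shown over a range of correlations.

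**Cost.** No new data and one degree of freedom. It is still a change to a registered trial whose enrolment began in August 2023, and under Definition of study conclusion any modification needs a prior favourable ethics committee opinion. The stated power will also look less favourable, because removing Day 0 removes the basis on which N = 24 was calculated.

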### Safety, tolerability, and blinding assessment

Adverse effects will be assessed using a questionnaire adapted from Antal et al. (59). Participants will be asked to complete the questionnaire after each session. The questionnaire includes items related to potential adverse effects such as headache, tingling, skin redness, neck pain, scalp pain, itching, drowsiness, difficulty concentrating, burning sensation, and acute mood change. In addition, other information regarding when the adverse event occurred, its duration, and where the discomfort is located will be recorded. Participants will quantify the severity of adverse effects as follows: (0) absent; (1) mild; (2) moderate; and (3) severe.

The questionnaire will also inquire about participants’ perception of whether they received active stimulation or not. For more details, see Supplementary materials S4.

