### Study design

The study will employ a within-subject, randomized, double-blind, and sham-controlled design. Clinical eligibility, including the dyslexia assessment, the neuropsychological assessment, and the psychopathological assessment will be evaluated on Day 0 (Baseline). Participants will be exposed to three conditions (Day 1, Day 2, Day 3): (A) a single active tDCS session; (B) a single active hf-tRNS session; and (C) a single sham tDCS or sham hf-tRNS session. Each condition will be separated from the other by a one-week interval to avoid carry-over effects (27). The ordering of conditions will be counter-matched among participants. After recruitment, participants will be allocated to one of six possible combinations of conditions (i.e., ABC, ACB, BAC, BCA, CBA or CAB). Stratified randomization will be performed by an independent researcher immediately after the participant completes the screening evaluation. This process will ensure assignment masking. Stratified randomization will use the minimal sufficient balancing method to prevent imbalances in baseline characteristics and will take into account participants’ demographics (e.g., age, IQ, and gender) and the severity of DD (calculated as the mean standard deviation between speed and accuracy in the text reading task) (45–48). The randomization information will be retained by an independent researcher until the data collection has been completed (Figure 1).

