### Protection of risks

To reduce any risks associated with tDCS/tRNS, participants will be closely monitored throughout the stimulation sessions and encouraged to report any discomfort. Should they experience uncomfortable scalp sensations or headaches, the stimulation will be immediately halted. All tDCS/tRNS sessions will be conducted and supervised continuously by a trained experimenter.

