Among the main purposes of the present study is to compare the safety and tolerability profile of tDCS and tRNS in pediatrics, in order to verify which intervention is safer and more suitable for use as standard-of-care intervention for children and adolescents with DD. While tES has been increasingly applied in developmental age, there are limited studies that have systematically investigated the safety and tolerability of tES in children and adolescents [(40, 86–88); for a review, see (41)], overall promoting tES as a safe method as for adults. Furthermore, while evidence suggests that tRNS is a safe and potentially less perceptible technique compared to tDCS (26, 36, 38), only one study has directly compared the safety and tolerability of the two techniques in children and adolescents (26), demonstrating that tRNS is less perceptible and potentially preferable in pediatrics. In particular, Berger et al. (26) documented a lower incidence of participants reporting adverse events with tRNS compared to tDCS (6 participants vs. 13 participants, respectively), particularly concerning the symptom “itching” (7% of sessions vs. 13% of sessions, respectively). Similarly, Pena and colleagues also observed a higher overall occurrence of minor adverse events in the tDCS group compared to the tRNS group. These initial findings align with prior studies by Ambrus and colleagues (38), who suggested in their conclusions that future research should explore alternative methods to the sham condition (such as placebo itching) to ensure better blinding integrity.

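### The only adverse-effect questionnaire described comes within minutes of stimulation, so the comparison supports immediate tolerability rather than the broader aim of showing which technique is safer

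*Protocol article*

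**What the plan says.** All references are to the protocol article.

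- **Timing.** Safety, tolerability, and blinding assessment: "Participants will be asked to complete the questionnaire after each session". Study design (text after Figure 1) breaks the session of about 35 minutes into 10 minutes of reading, 20 minutes of stimulation, and "5 min for the administration of the safety and blinding questionnaire after the stimulation session".
- **Content.** The items are scored 0 (absent) to 3 (severe) and include headache, drowsiness and mood change. The same section adds that "other information regarding when the adverse event occurred, its duration, and where the discomfort is located will be recorded".
- **During stimulation.** Protection of risks: "participants will be closely monitored throughout the stimulation sessions and encouraged to report any discomfort".
- **Between sessions.** Study design: "Each condition will be separated from the other by a one-week interval to avoid carry-over effects". No adverse-effect enquiry is described within that week, at the start of the next visit, or after Day 3.
- **Use of the data.** The Discussion calls the safety comparison one of the study's main purposes, "in order to verify which intervention is safer and more suitable for use as standard-of-care intervention for children and adolescents with DD". Statistical analyses and expected results sets a narrower hypothesis for safety against sham: "neither tDCS nor hf-tRNS will induce severe AEs or lead to dropouts due to intolerance to stimulation".

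**The concern.** The period of questioning is much shorter than the conclusion it is meant to support. Several listed items, among them headache, neck pain, skin redness, drowsiness, poor concentration and mood change, can begin or continue after a child has gone home. The article itself expects stimulation to act beyond the session. The Introduction describes aftereffects of tDCS, the Discussion chooses the tRNS frequency band for its lasting effect on excitability, and the one-week spacing is there to prevent carry-over.

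Two kinds of information are at risk. An effect that starts after the questionnaire leaves that session scored as absent on the form. An effect still present at the questionnaire is seen, but its end is not, so the requested duration is incomplete. Unrecorded late effects move every condition towards absent, which makes the techniques look more alike and more like sham. The Limitations section does not mention this; its remark on longitudinal monitoring concerns reading only.

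**Working it through.** **1. The plan's own figure.** The article computes nothing for safety. Its one computed figure is the sample size of 24. It reproduces with a repeated-measures ANOVA with m = 4 measurements, f = 0.25 and alpha = 0.05, if a correlation of 0.5 and full sphericity are assumed (neither is stated): lambda = N × m × f² / (1 − rho) = 24 × 4 × 0.0625 / 0.5 = 12, df = 3 and 69, power 0.817. It serves here only as the number of children; nothing in this point changes it.

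**2. Length of the enquiry.** Inputs from Study design: 20 minutes of stimulation, a 5-minute questionnaire slot, and one week between conditions.
- Close of enquiry after the start of stimulation: 20 + 5 = about 25 minutes.
- One week: 7 × 24 × 60 = 10,080 minutes.
- Share covered: 25 / 10,080 = 0.25%.

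**3. What is captured, by type of effect.**

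| Effect | Presence recorded | Duration recorded |
|---|---|---|
| Starts and ends before the questionnaire | yes | in full |
| Starts before, still present at the questionnaire | yes | only up to that moment |
| Starts after the questionnaire | no scheduled route described | no |

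**4. What a late-effect rate would mean.** The documents give no rate of delayed effects. Purely as an assumption, take 5% to 10% of active sessions, any severity, independent between children:
- Expected children per condition: 24 × 0.05 = 1.2; 24 × 0.10 = 2.4.
- Chance of at least one: 1 − 0.95^24 = 0.71; 1 − 0.90^24 = 0.92.

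These figures show only that late effects, if they occur at such rates, would probably arise in a sample of this size. They are not evidence that they do occur, and they say nothing about severe events.

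**5. Coverage of a repeat at the next visit.** A condition is followed by another visit when it stands first or second in the order. For condition A that holds in ABC, ACB, BAC and CAB, but not in BCA or CBA: 4 of 6 orders. The same count holds for B and C. With four children per order (assumed exact balance), each condition has 24 × 4/6 = 16 interval reports, 48 over the trial.

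**The case against.** **A later enquiry may exist elsewhere.** The schedule figure, the supplementary questionnaire and the full protocol are not shown, and an article condenses. This stands as a limit: one cannot infer that no later enquiry exists, only that none is described. But the timing itself is stated, in two places, so the point concerns a stated choice.

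**Duration is recorded, and questioning is not confined to five minutes.** A reader might infer that duration cannot be seen at all, or that nothing is noticed outside the questionnaire. The documents do not support that. The form records "when the adverse event occurred, its duration, and where the discomfort is located will be recorded", which is complete for effects that have ended by then; children are monitored during stimulation; and five minutes is the time to fill in the form, not the period it covers. The Withdrawal section and the emergency code also provide for adverse effects without limiting them to the visit, so spontaneous reports remain possible.

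**The formal hypothesis is narrow.** A reader might infer that missed late effects bias the finding of safety equal to sham. Mostly they do not. That hypothesis concerns severe events and intolerance dropouts, so a mild headache that evening does not bear on it, and a child who stays away because of intolerance is a dropout whenever the symptom began.

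**Much of the interest is immediate.** The motivation leans on itching, skin perception and blinding, in a proof-of-concept study of single sessions, and safety is not among the primary or secondary outcomes listed under Reading tasks. A questionnaire straight after the session suits that purpose. This stands, but the Discussion's aim goes further, to suitability as standard care.

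**Conclusion.** The point holds in a limited form. On the text as published, scheduled enquiry ends about 5 minutes after stimulation. Effects that start later have no described scheduled route of capture, and duration is truncated for those still present. The data can therefore compare tDCS, hf-tRNS and sham on immediate tolerability, but cannot by themselves establish which technique is safer in the sense of the Discussion. The formal safety hypothesis is exposed only to a delayed severe event that is neither volunteered nor followed by dropout.

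The practical size cannot be given, because no rate of delayed effects is stated; the 1.2 to 2.4 children per condition rest wholly on an assumed 5% to 10%. The reading outcomes and the sample size are unaffected. The conclusion also assumes that the material not shown contains no later enquiry; if it does, the article need only say so.

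**What to change.** 1. Repeat the adverse-effect questionnaire, on the same 0-3 scale, at the start of Day 2 and Day 3, before the pre-stimulation reading. It should cover the interval since the last session, be attributed to that session's condition, and complete the duration of anything still present at the last form.
2. Report these interval data separately from the immediate reports, stating that each condition has them in about two thirds of children.
3. A contact after Day 3 is optional and needs care: Study design discloses the condition order at the end of Day 3, so a later contact would collect unblinded reports. Either make it before disclosure or report it separately as unblinded.
4. If none of this is added, limit the safety conclusions in Statistical analyses and in the Discussion to effects during and immediately after a single session.

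**Cost.** Two short enquiries per child at existing visits (2 × 24 = 48), with no new visit and no change to stimulation, reading outcomes or sample size. The drawback is recall: over a week, children will remember severity and duration imprecisely and report unrelated complaints. The blinded interval after sham gives a reference rate for the latter. The wording change in item 4 costs nothing.
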